## Abstract

**Background:**

Type 2 diabetes is a prevalent chronic condition, particularly among older adults, and is associated with significant morbidity, mortality, and health care costs. Effective disease self-management is crucial for achieving glycemic control and preventing complications.

**Objective:**

This pilot study aims to evaluate the effectiveness of a structured, 5-week training program in improving eHealth literacy among older adults with type 2 diabetes and to assess its impact on health literacy, self-efficacy, psychological well-being, and clinical outcomes.

**Methods:**

In total, 200 community-dwelling adults aged ≥60 years with type 2 diabetes, a Mini-Mental State Examination score ≥24, a Geriatric Depression Scale score <9, and a low eHealth Literacy Scale score (≤29) will be recruited. Participants will attend five 90-minute weekly training sessions combining didactic and interactive modules focused on health literacy, diabetes self-management, and the use of digital tools. Assessments will be performed at baseline (T0), post intervention (T1), and at 1-month (T2) and 6-month (T3) follow-up. The primary outcome will be the change in eHealth literacy, as measured by the eHealth Literacy Scale, from baseline to post intervention. In addition, a wide range of secondary outcomes will be examined to capture the program’s multidimensional impact: improvements in general health literacy, self-efficacy in diabetes management, psychological well-being, and quality of life; reductions in diabetes-related emotional distress, body weight, and BMI; and better metabolic control, as measured by hemoglobin A_1c_ and lipid profiles. Finally, participants’ experiences, satisfaction, and perceived benefits will be explored to inform the future scalability and refinement of the program. A prestudy will be conducted, involving stakeholders, older adults, and caregivers, to refine the training content using co-design techniques. Descriptive statistics will be used to summarize sample characteristics. Preintervention and postintervention changes will be evaluated using 2-tailed paired *t* tests or their nonparametric equivalents, with repeated-measures models applied to follow-up data. A *P* value <.05 will indicate statistical significance.

**Results:**

The prestudy phase began in April 2025. Improvements in both health literacy and eHealth literacy are expected to be observed among participants, as assessed through validated instruments administered before and after the intervention.

**Conclusions:**

The Joint Action on Cardiovascular Diseases and Diabetes (JACARDI) study provides a structured and participatory approach to addressing the digital divide in chronic disease management among older adults. By focusing on personalized, evidence-based training, the study offers a promising model for empowering patients and improving health outcomes through enhanced digital and self-management competencies.

## Introduction

### Background

Diabetes is a chronic disease that affects people of all ages worldwide. It occurs when the pancreas does not produce enough insulin or when the body is unable to effectively use the insulin it produces. The former is known as type 1 diabetes, while the latter is known as type 2 diabetes. According to the World Health Organization (WHO), diabetes represents a global epidemic [1]. In fact, the number of people with diabetes has quadrupled since 1980 and is expected to continue growing. For example, in 2024, there were over 588 million individuals aged 20 to 79 years with diabetes worldwide, accounting for around 11% of all adults in this age group [2]. In Italy, slightly less than 5% of adults aged 18 to 69 years reported a diagnosis of diabetes in the biennium 2022‐2023; this percentage rose to almost 9% among individuals aged 50 to 69 years [3].

Given the widespread and growing prevalence of diabetes, it is essential to consider not only its health impact but also its broader complications and economic consequences. Beyond its health implications, the rising prevalence of diabetes imposes a significant economic burden on health care systems, accounting for around 12% of the total global health spending [2]. Due to their complexity and long-term treatment needs, complications resulting from poor diabetes management, including cardiovascular disease, kidney failure, and amputations, significantly increase the financial pressure on health systems [4].

Therefore, investing in effective prevention, education, and management strategies is a public health and economic priority [5].

Furthermore, while premature mortality due to other major noncommunicable diseases is decreasing, early deaths due to diabetes are increasing: there was a 5% increase between 2000 and 2016. Missed diagnosis or inadequate management of diabetes can lead to serious risks of debilitating and irreversible complications, including severe damage to the heart, eyes, kidneys, and nerves, which increases the risk of limb amputation, vision loss, and premature death [1].

One of the most important behavioral and therapeutic goals in the treatment of diabetes is glycemic control, which is a major aspect for reducing morbidity and mortality in people with type 2 diabetes (the most common type) [6].

At the core of diabetes management, glycemic control primarily involves patient self-management [7], which is achievable when a person with diabetes acquires the necessary knowledge (such as healthy nutrition, physical activity, blood glucose monitoring, and adherence to medication) and skills (eg, problem solving and healthy coping mechanisms) for behavior modification to better cope with the disease [8,9]. All these self-management behaviors fundamentally rely on health literacy as a foundational skill, as the ability to access, understand, and apply health information determines how effectively people with diabetes can engage in prevention, treatment adherence, and long-term disease control [10].

Indeed, people with lower health literacy levels tend to experience poorer overall health, higher rates of hospitalization and mortality, a lower ability to manage chronic diseases, and higher health care expenditures. In contrast, those with higher health literacy levels have a higher probability of using available health care services and making well-informed health care decisions [11]. Therefore, while a low level of health literacy may hinder the development of diabetes self-management skills [12], a high level is associated with confidence in diabetes self-management [13].

In this regard, studies have shown that interventions can improve glycemic control, quality of life, diabetic complications [8], and knowledge and skills of diabetes management [14].

However, despite these proven benefits, access to structured and effective self-management education remains uneven and inadequate in many cases, particularly among the most vulnerable populations with low socioeconomic status, limited education, language barriers, or limited access to health infrastructure [15]. These individuals often face additional difficulties in acquiring, understanding, and applying health information and, as a result, may be less likely to engage in sustained self-care behaviors, adhere to treatment regimens, or benefit from early prevention strategies. Therefore, addressing these gaps is essential to ensure that self-management interventions reach their full potential in improving population-level disease control.

However, digital exclusion can contribute to health inequalities and poorer health outcomes, particularly affecting older adults, marginalized groups, and people with disabilities, who have fewer opportunities to access or use digital health platforms. In response, 75% of WHO European Member States with digital health strategies have prioritized improving digital literacy and ensuring equitable access to fast, safe, and reliable internet [16]. Therefore, addressing eHealth literacy and digital inclusion is important in supporting effective diabetes self-management.

### Goal of the Study

This paper presents the protocol for the Joint Action on Cardiovascular Diseases and Diabetes (JACARDI) field trial, which aims to reduce the burden of cardiovascular disease and diabetes in European Union (EU) countries, at both the individual and societal levels. JACARDI is designed to integrate validated best practices and cost-effective interventions across countries and regions through transnational pilot initiatives, thereby complementing and reinforcing existing policies and programs. JACARDI will enhance cross-national collaboration, maximizing the exploitation of lessons learned through a clear strategy; engaging groups of interest; and promoting integration and sustainability of approaches to achieve high-level impact, including the implementation of effective interaction, cooperation, and cocreation between science and policy. In particular, this pilot study focuses on improving health literacy and awareness of cardiovascular disease and diabetes risks and risk factors, at both the individual and societal levels. It aims to reach people living with cardiovascular disease and diabetes and their care providers and to improve service pathways, self-management, and labor participation.

## Methods

### Field Trial

The JACARDI trial is a multicenter study coordinated by the Istituto di Ricovero e Cura a Carattere Scientifico-Istituto Nazionale di Riposo e Cura per Anziani (IRCCS INRCA) and conducted also at the Clinic of Endocrinology and Metabolic Diseases of the Azienda Ospedaliero-Universitaria delle Marche. Adopting a blended approach combining didactic and interactive training, the study primarily aims to improve eHealth literacy in older adults with type 2 diabetes, thereby promoting independent living and reducing the risk of health deterioration and impaired quality of life. The study consists of five phases: (1) recruitment and screening, (2) baseline assessment (T0), (3) a 10-week educational intervention, (4) postintervention assessment (T1), and (5) follow-up evaluations at 1 month (T2) and 6 months (T3).

Prior to the trial, a prestudy will be conducted to co-design and finalize the training content. A group of volunteers whose characteristics are similar to those of the target population will participate in focus groups to refine the training content and practical aspects prior to recruitment. The protocol was developed in accordance with the SPIRIT guidelines (Checklist 1).

Figure 1 shows the design of the JACARDI study.

**Figure 1. F1:**
[figure not shown]
Flowchart of the study design, illustrating the screening process, the intervention and follow-up assessments, and the final sample analyzed.

### Prestudy Phase for Refinement of the Training Content

To evaluate the core concepts, strategies, and format for the pilot study, a preliminary prestudy will be conducted with a range of stakeholders, as outlined below:

Context analysis: A total of 10 semistructured interviews will be conducted with local experts (ie, service providers, regional and local policymakers, facility managers, and nongovernmental organizations) and health professionals (ie, medical doctors, nurses, psychologists, dietitians, and physiotherapists) to identify the enablers of and potential barriers to the pilot implementation, on the basis of the Consolidated Framework for Implementation Research (CFIR).Focus groups: Two focus groups, each comprising 10 older adults, and one focus group consisting of 10 informal caregivers (not necessarily linked to the patients participating in the study) will be conducted to assess the validity of the proposed training concepts. Co-design techniques such as 6-3-5 brainwriting, simplified scoring, and open discussion will be used to refine the training content and practicalities.

The focus groups and interviews will be audio-recorded and subsequently transcribed in full. Then, the transcripts will be coded and analyzed using thematic analysis to identify key patterns and themes. Two researchers who will compare and discuss their findings to ensure consistency and credibility will collaboratively conduct the analysis and interpretation of results. Any discrepancies in interpretation will be resolved through discussion with a third senior researcher. The involvement of participants with a range of roles will contribute to the validity of findings. These procedures will enhance the rigor and trustworthiness of the co-design phase.

Indeed, the results of the prestudy phase will facilitate the refinement of the training sessions’ core content, which will be assessed through the pilot intervention. Specifically, the content, format, and delivery methods of the intervention will be adapted according to the themes that emerge from the focus groups and interviews. This will ensure that the final program reflects the needs, preferences, and lived experiences of the target population and stakeholders. The inclusion and exclusion criteria set for the JACARDI trial will be adopted in the prestudy phase as well, with the objective of involving older patients who exhibit the same characteristics as those in the final trial. Regarding caregivers and other stakeholders such as policymakers, there are no specific criteria in place other than being a carer of a diabetic person and working in the health policy sector, respectively.

### Participant Recruitment

The recruitment will be conducted in the selected centers under the coordination of the IRCCS INRCA. Following a 2-week reflection period, individuals who confirm their wish to participate in the research in writing or verbally, after having read the information letter and the consent form received by email, will be invited by the investigator to consult a doctor in the 3 months preceding the start of the research. The doctor volunteering to carry out the inclusion visits will first provide the participant with the information letter and 2 consent forms. After the participant and the doctor carefully read and sign the consent forms, the doctor will use anamnesis, the Mini-Mental State Examination (MMSE), the Geriatric Depression Scale (GDS, 5-item version), and the eHealth Literacy Scale (eHEALS) to ascertain the participant’s eligibility for the research study. This medical examination will take place before the study begins. Participants who sign the consent form but for whom the fulfillment of the inclusion criteria is not confirmed by the doctor will not be included in the research.

To ensure participants’ ability to engage actively in the training activities and complete the assessments, certain criteria were applied to assess cognitive health (MMSE score ≥24) and physical health (eg, absence of severe mobility limitations, advanced neurodegenerative diseases, or significant sensory impairments). These requirements are intended to minimize participant burden, ensure safety during in-person group sessions, and reduce attrition due to difficulties in attending sessions or completing questionnaires. While this approach improves the internal validity and feasibility of the pilot implementation, it may limit the representativeness of the sample with respect to the broader population of older adults with type 2 diabetes. The inclusion and exclusion criteria are reported in Textbox 1.

Textbox 1.Inclusion and exclusion criteria for patients.

**Exclusion criteria**
Failure to meet the inclusion criteriaSimultaneous participation in other studiesLack of written informed consentHistory of a myocardial infarction or stroke within the past 6 monthsPainful arthritis, spinal stenosis, amputation, painful foot lesions, or neuropathy, limiting balance and mobilityUncontrolled hypertensionAdvanced Parkinson disease or other neuromuscular disorderDiagnosis of metastatic cancer or treatment with immunosuppressive therapySignificant visual or hearing impairment

Following the medical visit, the investigator will contact the potential participant by email or telephone to discuss the study and confirm their interest in participation. At this stage, detailed information about the study procedures will be provided, and written informed consent will be obtained before any study-related activities are initiated. The schedule for the visits and the procedures for conducting the research at the participant’s home will then be agreed upon according to participant availability. When recruitment is complete, participants included in the study will undergo all routine clinical investigations, such as collection of blood samples to assess their glycemic and lipid profiles and measurement of BMI. In addition, a researcher will perform the preliminary evaluation (T0). The scales described in Textbox 2 will be administered, and then an interview will be conducted. The participant will undergo training sessions at the study centers with the other study participants. After 10 weeks, the final evaluation will be conducted (T1). Participants will be required to complete a series of questionnaires, the details of which can be found in Table 1. During this phase, blood sample collection and BMI measurement will not be performed.

During the 2 follow-up visits (1 month and 6 months following the conclusion of the intervention), any alterations in the patient’s medical history will be recorded. All routine clinical investigations and all planned assessment scales will be administered. Blood sample collection to assess the glycemic and lipid profiles and BMI measurement will be performed exclusively at T3.

Textbox 2.Outcomes of the study.
**Primary outcomes**
Improvement in eHealth literacy, assessed using the eHealth Literacy Scale (eHEALS) [17]
**Secondary outcomes**
Improvement in self-efficacy, evaluated using the Diabetes Management Self-Efficacy Scale (DMSES) [20]Reduction in emotional distress related to diabetes, measured using the Problem Areas in Diabetes Questionnaire (PAID) [21]Improvement in psychological well-being, assessed using the Psychological Well-Being Scale (PWB) [22]Improvement in quality of life (QoL), assessed using the EQ-5D-5L Visual Analog Scale (VAS) [23] and 12-item Short Form Health Survey (SF-12) [24]Reduction in body weight (measure routinely collected at the Diabetology Unit)Reduction in BMI (measure routinely collected at the Diabetology Unit)Improvement in the glycemic profile (glycated hemoglobin; measure routinely collected at the Diabetology Unit)Improvement in the lipid profile (directly related to cardiovascular risk; measure routinely collected at the Diabetology Unit)Collection of information about the participants’ experience with the training, their level of satisfaction, any benefits they have experienced, and any improvement suggestions, using an ad hoc questionnaireImprovement in health literacy, assessed using the 16-item European Health Literacy Survey Questionnaire (HLS-EU-Q16) [25]

**Table 1. T1:** Tools and dimensions of the protocol.

Dimension	Tool	R^a^	T0^b^	T1^c^	T2^d^	T3^e^
Cognitive status	MMSE^f^	X	—^g^	—	—	—
Psychological status	GDS^h^ 5-item version	X	—	—	—	—
General information	Sociodemographic questionnaire	X	—	—	—	—
Quality of life	EQ-5D-5L VAS^i^, SF-12^j^	—	X	X	X	X
Psychological well-being	PWB^k^ (18 items)	—	X	X	X	X
eHealth literacy	eHEALS^l^	X	—	X	X	X
Health literacy	HLS-EU-Q16^m^	—	X	X	X	X
Diabetes-related emotional distress	PAID^n^	—	X	X	X	X
Self-efficacy	DMSES^o^	—	X	X	X	X
Training experience	Ad hoc questionnaire	—	—	—	—	X

a R: recruitment.

b T0: first evaluation.

c T1: final evaluation.

d T2: follow-up 1 month after the end of the training.

e T3: follow-up 3 months after the end of the training.

f MMSE: Mini-Mental State Examination.

g not applicable

h GDS: Geriatric Depression Scale.

i VAS: Visual Analog Scale.

j SF-12: 12-item Short Form Health Survey.

k PWB: Psychological Well-Being Scale.

l eHEALS: eHealth Literacy Scale.

m HLS-EU-Q16: 16-item European Health Literacy Survey Questionnaire.

n PAID: Problem Areas in Diabetes Questionnaire.

o DMSES: Diabetes Management Self-Efficacy Scale.

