From a methodological point of view, the study adopts a robust evaluation framework using validated tools and multiple follow-up time points, thereby enabling both short-term and midterm outcome monitoring. The use of both subjective (eg, questionnaires) and objective (eg, glycemic and lipid profiles) measures allows for a multidimensional evaluation of the intervention’s impact.

However, it is important to acknowledge some limitations. This being a pilot study, the generalizability of the results may be constrained by the specific characteristics of the local settings and participants. Moreover, despite efforts made to personalize the intervention, its scalability across different health care systems and sociocultural environments may require further adaptations. Potential barriers include disparities in digital access or digital literacy among older adults, as well as local infrastructure constraints that may affect intervention delivery. To address these issues, the study will employ a blended training format combining digital and in-person components and provides technical support and guidance to participants. Feedback will be collected to inform future adaptations for broader implementation. In addition, the exclusion criteria—particularly the exclusion of individuals with severe mobility limitations, advanced Parkinson disease, and significant visual or hearing impairment—may restrict the external validity of the findings. The establishment of these criteria was deemed necessary to ensure the attendance of all participants to the requisite training sessions and to facilitate their effective engagement with the digital tools that will be introduced. Nevertheless, they also exclude subgroups that may be among the most vulnerable to poor digital health engagement. It is recommended that future studies consider tailored strategies (eg, home-based or caregiver-assisted training, accessible digital interfaces) to reach these populations and evaluate whether adapted interventions can address their specific needs.

Despite these challenges, the JACARDI pilot study represents a valuable contribution to the growing field of digital health literacy and chronic disease self-management.

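### HbA1c, lipid, weight and BMI changes to T3 are uncontrolled and read as programme impact, but no stated analysis uses drug changes in between

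*Protocol article*

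**What the plan says.** **Outcomes.** Textbox 2 lists, among the secondary outcomes, "Improvement in the glycemic profile (glycated hemoglobin; measure routinely collected at the Diabetology Unit"), "Improvement in the lipid profile (directly related to cardiovascular risk; measure routinely collected at the Diabetology Unit") and "Reduction in body weight (measure routinely collected at the Diabetology Unit"). BMI is worded in the same way as weight.

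**Timing.** Under Participant Recruitment (text after Textbox 1), bloods and BMI are taken once recruitment is complete, are not taken at T1, and are repeated only at T3. At the two follow-up visits "any alterations in the patient’s medical history will be recorded". Drugs are not named there, and no use of the record in an analysis is given.

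**Analysis.** The Abstract says "Preintervention and postintervention changes will be evaluated using 2-tailed paired" t tests or their nonparametric equivalents, with repeated-measures models for follow-up data. The Statistical Analysis section names paired and independent tests and their rank-based versions, with no treatment term. No comparator arm is described.

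**Interpretation.** The Objective is "to assess its impact on health literacy, self-efficacy, psychological well-being, and clinical outcomes". The Abstract counts "better metabolic control, as measured by hemoglobin A_1c_ and lipid profiles" among the outcomes that capture the programme's impact. The Discussion says that using both questionnaires and glycemic and lipid profiles "allows for a multidimensional evaluation of the intervention’s impact". Its limitations cover generalizability, scalability, digital access and the exclusion criteria. They mention neither the missing comparator nor changes in treatment.

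**The concern.** Participants have type 2 diabetes, and their metabolic measures come from a Diabetology Unit's routine care. Months pass between the two measurements, and prescriptions can change in that time. A paired T0-to-T3 difference adds any effect of training to any effect of a drug started, stopped, increased or reduced, and the plan as described has no step that separates or even displays the two.

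If net treatment was intensified, the result could be credited to literacy training when it came from prescribing. If net treatment was reduced, a real benefit could be hidden. HbA1c and lipids are the outcomes that the Discussion presents as objective evidence, so readers are likely to give them weight. The primary outcome, eHEALS, is not affected.

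**Working it through.** **1. The plan's own figure.** The only sample size calculation is for eHEALS: effect size 0.48, 1-tailed alpha 0.05, power 90%. An exact paired t test gives N = 39 (power 0.903), as stated. The inflation to 45 matches 39 x 1.15 = 44.85; dividing by 0.85 gives 46. None of this concerns HbA1c, lipids or weight, for which the article states no effect or SD. The steps below are therefore illustrations.

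**2. Length of the window.** The sections disagree. The Abstract gives a 5-week programme, while the Field Trial and Intervention sections give 10 weeks. T3 is 6 months after training in the Abstract, Field Trial, Participant Recruitment and Outcomes sections, but 3 months in Table 1, footnote e. With 4.35 weeks per month:
- 10 weeks + 6 months: 2.3 + 6 = 8.3 months
- 10 weeks + 3 months: 2.3 + 3 = 5.3 months
- 5 weeks + 6 months: 1.1 + 6 = 7.1 months
- 5 weeks + 3 months: 1.1 + 3 = 4.1 months

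**3. Shift in the mean with no training effect.** Let f_up be the share intensified, with mean fall e_up, and f_down the share reduced, with mean rise e_down:

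mean change = -(f_up x e_up) + (f_down x e_down)

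The second term is why the direction is not fixed: equal shares and sizes cancel. With f_down = 0, and shares and effects that are assumptions (not in the documents):
- 10%, 0.5 points: 0.10 x 0.5 = 0.05 fall
- 20%, 0.8 points: 0.20 x 0.8 = 0.16 fall
- 30%, 0.8 points: 0.30 x 0.8 = 0.24 fall

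**4. Smallest mean change that reaches P<.05.** Applying the stated 15% dropout to the planned 200 gives n = 200 x 0.85 = 170, with t(0.975, 169 df) = 1.974. The threshold is 1.974 x SD / sqrt(170), where sqrt(170) = 13.04:
- SD 0.8: 0.121
- SD 1.0: 0.151
- SD 1.2: 0.182

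**5. Chance of P<.05 with no training effect.** Two-sided paired t test, noncentral t with noncentrality (mean change) x sqrt(170) / SD:

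| Scenario | Mean fall | SD 0.8 | SD 1.0 | SD 1.2 |
|---|---|---|---|---|
| 10%, 0.5 points | 0.05 | 13% | 10% | 8% |
| 20%, 0.8 points | 0.16 | 74% | 55% | 41% |
| 30%, 0.8 points | 0.24 | 97% | 88% | 74% |

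The nominal rate is 5%.

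**6. What a stable-therapy analysis would cost in precision.** If 20% to 30% have a relevant drug change, 170 x 0.80 = 136 to 170 x 0.70 = 119 remain. At SD 1.0 the threshold moves from 0.15 to about 0.17 to 0.18.

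**The case against.** **A condensed article leaves such detail elsewhere.** How medication is captured may well be set out in the full protocol, the case report form or the SAP. The inclusion doctor takes an anamnesis, and changes in medical history are recorded at both follow-up visits; either could include drugs. This stands as far as recording goes: a reader might infer that drug data are not collected, and the article does not show that. Table 1 is no evidence for it either, since it lists screening tests and questionnaires and also omits HbA1c, lipids, weight and BMI. The objection does not reach the impact reading of an uncontrolled change, which the article itself states.

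**Direction and size are assumed.** A reader might infer that the bias must be favourable. The documents do not support that: drugs can be stopped or reduced as well as started, and Textbox 1 sets no poor-control threshold at entry. Nor is it right that 20% intensified would by itself produce a significant result; at SD 1.0 the chance is 55%. The plan also allows Bonferroni or Holm correction where necessary. Bonferroni over the ten secondary items would raise the SD 1.0 threshold to 0.218 and cut that chance to 23%. All of this stands.

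**Drug changes may be part of the effect.** Module II covers treatment management and poor adherence, and the Introduction links higher literacy to service use and better-informed decisions. Excluding participants whose drugs changed could remove part of a real effect. This stands too, and it limits what a stable-therapy subset can be used for.

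**The root problem is the missing comparator.** True, and drug change is only one rival explanation. It is, however, one that can be described from clinic records.

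**Conclusion.** The concern holds in a limited form. The metabolic secondary outcomes are single-group changes over several months of routine diabetes care, the article interprets them as impact, and no stated analysis uses drug changes. Treatment adjustment can add to the measured change or mask it, and the plan as described gives no means of telling which.

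The size is unknown. Under assumed rates, HbA1c effects and SDs, with n = 170, no multiplicity correction and changes in one direction only, the chance of a significant HbA1c fall without any training effect runs from 8% to 13% in the mildest scenario to 74% to 97% in the strongest one shown. The documents do not support the claims that drug data are certainly missing, that the bias is certainly favourable, or that a spurious significant result is certain. The point concerns secondary outcomes and leaves the eHEALS analysis untouched.

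**What to change.** 1. Extract from the clinic record, for the interval T0 to T3, starts, stops, increases and reductions of glucose-lowering, lipid-lowering and weight-altering drugs.
2. Keep the all-participant T0-to-T3 change as the main result for each metabolic outcome.
3. Report beside it how often each kind of drug change occurred and, as a sensitivity analysis, the change in participants without a drug change relevant to that outcome.
4. Describe all these outcomes as uncontrolled changes rather than effects of training, and name the missing comparator and treatment changes in the limitations.
5. Do not make agreement in the stable-therapy subset a condition for wording such as improved metabolic control. The subset is selected after baseline, and drug changes may lie on the pathway from training to outcome.
6. Reconcile the T3 timing (6 months in the text, 3 months in Table 1, footnote e) and the programme length (5 weeks in the Abstract, 10 weeks in the Methods), since together they set the window for drug changes.

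The cost is a short chart extraction covering two scheduled assessments and one extra analysis per outcome. The downside is a smaller, selected subset. Even with these data, a causal reading without a comparator is not restored.
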